## Abstract

**Background:**

Post-COVID-19 syndrome (PCS) presents in a multitude of ways, with fatigue, physical constraints, and diminished quality of life being common symptoms. It is becoming increasingly clear that unimodal behavioral interventions do benefit all PCS patients. Adherence to and response to isolated psychotherapy or physical activity interventions vary greatly, with certain patients benefit more from one form of therapy, or even a combination, than others do. The study aims to compare the effects of a single exercise therapy, psychotherapy, and a combination of both therapies.

**Methods:**

The study will be conducted as a prospective, randomized controlled, open-label trial with 3 treatment arms (exercise therapy, psychotherapy, and combined therapy). According to the sample size calculation, 65 participants will be enrolled in each group. The primary outcome is the change of PCS fatigue symptoms from baseline to 3 months, estimated by the Fatigue Assessment Scale. Secondary endpoints include changes in further measures of fatigue (Chalder Fatigue Skala, Multidimensional Fatigue Inventory, Post-exertional Malaise Scale, Bell Scale), health-related quality of life (Short Form-36 and Brief Illness Perception Questionnaire), anxiety and depression (Hospital Anxiety and Depression Scale), and work ability (Work Ability Index). The intervention lasts for 3 months and includes online therapy sessions of 50 min every 2 weeks or in case of lack of concentration or fatigue this could be split to two 25-min sessions (all equating to a total of 300 min of specialist care). The psychotherapy adopts a short-term and coping-oriented approach based on the unique requirements of each patient from a psychotherapeutic perspective. Exercise therapy involves a personalized physical activity plan customized to suit the patient’s requirements, with tracking day-to-day physical activity along with daily moderate endurance and strengthening workouts. An ANCOVA model, including the stratification factors sex and BMI, will be used for the primary analysis of Fatigue Assessment Scale. Significance tests will be based on the group differences in least square means and corresponding 95% CIs.

**Discussion:**

Due to the current relevance of the issue, the unclear evidence so far, and the lack of appropriately powered randomized studies, it is crucial to assess potentially effective concepts for treating patients with PCS. Future therapy decisions will benefit from answering the question of whether combined therapies hold a significant advantage over unimodal therapeutic approaches, as well as identifying predictors that indicate an advantage of certain therapies for particular patients.

**Trial registration:**

ClinicalTrials.gov NCT06042751. Registered on 21 September 2023.

**Supplementary Information:**

The online version contains supplementary material available at 10.1186/s13063-025-08968-7.

## Introduction

### Background and rationale {6a}

A post-COVID-19 syndrome (PCS) as defined by the World Health Organization (WHO) “occurs in individuals with a history of probable or confirmed SARS-CoV-2 infection, usually 3 months from the onset of COVID-19 with symptoms that last for at least 2 months and cannot be explained by an alternative diagnosis” [1]. Estimates indicate that PCS occurs in up to 10% of all infected persons, affecting not only severely ill patients but also those with a mild or even asymptomatic course [1–3]. The courses of PCS are varied, but all lead to limitations in everyday life due to chronic fatigue, exercise intolerance, dyspnea, neurocognitive impairments, muscle pain, sleep disorders, and/or headaches [4].

To date, few randomized controlled trials (RCT) have been published on the efficacy of physical rehabilitation on fatigue in PCS patients. A current meta-analysis lists three controlled studies with one of them showing a between-group improvement, with a pooled significant decrease in fatigue severity [5]. More recent RCTs either showed differences in fatigue between exercise and usual care groups after 4 to 12 weeks of intervention [6, 7] or no significant effects, despite some indices of improved physical performance [8, 9].

Research on the effectiveness of psychotherapeutic approaches in patients with PCS-related fatigue is still limited, with some trials currently ongoing. A pilot study by Huth et al. shows potential to improve fatigue as well as other psychosocial outcomes in patients with PCS [10]. In 2023, a study presenting a psychotherapeutic intervention to treat fatigue in patients with sarcoidosis was published. The online mindfulness-based cognitive behavioral therapy approach was able to significantly improve fatigue, anxiety, depression, and overall health status in patients with sarcoidosis-associated fatigue [11].

Taken together, current data suggests that psychotherapeutic and exercise therapy concepts are beneficial in some but not all conducted RCTs. Nevertheless, a combination of both therapy approaches should have a greater effect on fatigue than unimodal therapies, a research question not addressed so far. In this context, a comprehensive care model should be home-based and supported by personal coaching via telemedicine, which allows reaching as many patients as possible at a low threshold [7, 12–14]. Therefore, the hypothesis of this randomized three-arm study is that 3 months of individual, telemedicine-supported therapy, which combines psychotherapy and exercise contents, improves fatigue more than psychotherapy or exercise therapy alone. An additional aim of the study is to investigate predictors for the responsiveness of the three conducted therapy approaches.

### Objectives {7}

The primary objective of the study is to show that 3 months of individual, combined psychotherapy and exercise therapy improve fatigue more than psychotherapy or exercise therapy alone.

Another aim is to investigate predictors for the responsiveness of psychotherapy or exercise therapy or the combination of both.

### Trial design {8}

This is a randomized, controlled, three-arm, open-label, monocentric intervention trial to demonstrate superiority of a combined therapy for PCS fatigue symptoms over monotherapeutic approaches. PCS patients will be randomized in a 1:1:1 ratio stratified by sex (male/female) and body mass index (BMI) (< 30/≥ 30 kg/m^2^) to the 3 treatment groups.

## Methods: participants, interventions, and outcomes

### Study setting {9}

The baseline assessment takes place at Hannover Medical School, the university hospital in Hannover, Lower Saxony, Germany, which is the only study side. The study intervention will be performed telemedically by the therapists based at Hannover Medical School.

### Eligibility criteria {10}

This study will include participants who are 18 years of age or older, have been diagnosed with COVID-19 disease by real-time quantitative reverse transcriptase polymerase chain reaction (PCR) or antibody testing, and have experienced persistent fatigue for more than 3 months with a Fatigue Assessment Scale (FAS) score of ≥ 22. Participants currently enrolled in another interventional study, those with clinically relevant acute or chronic infections or organ damage caused by COVID-19, or those with suicidal tendencies or severe mental illness (such as mania or the acute phase of schizophrenia) requiring acute treatment are not eligible for this study. Participants who are unable to participate in the physical training intervention due to severe illnesses or functional limitations, as determined by the examining study doctor, will also be ineligible to participate.

### Who will take informed consent? {26a}

Informed consent is obtained by a trained and delegated physician (study investigator). The physician informs the patient about the objective, content, period, possible risk and harms, and data protection regulation of the study. Patients meeting the eligibility criteria receive both an oral explanation of the study and a participant information sheet with a participant consent form (see supplementary material 1 and 2 for original language and english language, respectively). Written informed consent is obtained prior to inclusion by discussing the nature, objectives, possible adverse events, and all other unresolved issue associated with the participation in the study. A copy of the information sheet and the signed and dated consent form are supplied to the patient providing written consent.

### Additional consent provisions for collection and use of participant data and biological specimens {26b}

N/A: only data available in the electronic medical record of the patients are collected for the purposes of this trial. No additional consent provisions are needed.

## Interventions

### Explanation for the choice of comparators {6b}

PCS is a complex condition in which pathophysiological processes have not been understood yet. At the same time PCS presents itself in many different symptoms and effects on daily life. This situation calls for holistic therapeutic approaches that target many different symptoms. Based on the rational that a combination of therapeutic interventions (psychotherapy and exercise therapy) addresses different effect mechanisms, a synergistic effect and an improved outcome are expected from the combination therapy. To be able to show this synergistic effect, monotherapeutic psychotherapy and exercise therapy were chosen as comparators.

### Intervention description {11a}

The study consists of three arms, each including 300 min of online therapy sessions over a period of 3 months, and a follow-up period of 3 months (6 months after BSL). The therapy consists of 300-min online intervention with 50-min sessions every 2 weeks (alternatively up to 12 × 25 min every week). The interventions are led by an exercise scientist and a psychological psychotherapist, respectively.

In the exercise therapy intervention, an individual exercise plan will be developed during the first online session based on the results of the aptitude test and the participant’s descriptions and routines. This exercise plan includes managing daily activities, a heart rate limit, moderate endurance and strength exercises, as well as stretching and relaxation exercises. To account for the physical inactivity caused by fatigue in many participants, light strengthening exercises (e.g., chair squats and wall push-ups) and shorter endurance exercises (e.g., walking, ergometer training, Nordic walking, cycling) will be usually performed at the beginning. If participants are currently receiving therapy, such as regular physiotherapy or ergotherapy, this will be integrated into the exercise plan and planned around it. The exercise plan aims to increase the frequency of strength and endurance training stimuli and to adjust the intensity to individual circumstances without causing overload or crashes. The activities are recorded using a wearable device. To ensure subjectivity of the intensities, the patients will keep a training diary during the intervention, in which the subjective feeling of exertion is assessed using the Borg scale and the daily feeling in the morning and in the evening (scale 1–10) is documented. During therapy sessions, activities will be discussed and exercise plans and the time between sessions will be considered. This includes wearable data, training diaries, sleep patterns, recovery, and existing therapies such as physiotherapy and occupational therapy. Other strenuous activities, such as cognitive activities, will also be taken into consideration as well as the physiology of training, fatigue, and recovery. The exercise therapy aims to improve reduced resilience and fatigue without overwhelming patients with volume or intensity. This will be achieved through a comprehensive approach that allows patients to engage in continuous, daily physical activity.

In the psychotherapeutic intervention, a modularized, coping-oriented short-term therapy based on the individual needs of the patient will be performed taking into account the specific deficits identified in the psychosomatic evaluation at baseline. The sessions focus on the following topics: (1) psychoeducation, (2) mindfulness regarding one’s own stress limits, (3) time and energy management based on self-observation to prevent crashes, (4) improving self-care and resources, (5) differentiate between helpful and less helpful coping strategies, and (6) consideration and treatment of mental comorbidity.

Within the sessions, starting points will be identified with the patients, which the patients can work on independently between sessions.

In the combined intervention, 12 sessions à 25 min will be performed alternating between psychotherapy and exercise therapy. The contents of the interventions are the same as described; however, due to the same amount of therapy in all three study groups, the treatment content in the combined study group is conveyed in a condensed form.

### Criteria for discontinuing or modifying allocated interventions {11b}

One or more of the following circumstances may lead to premature termination of the study for an individual subject: withdrawal of the subject’s consent, occurrence of an exclusion criterion, therapy discontinuation by the patient (not attending therapy visits or documenting discussed therapy contents), and other circumstances that would to lead to worsening of PCS symptoms if continuing the study. For the benefit and interest of the participant, the investigator can terminate study participation at any time if serious side effects or other unforeseeable circumstances occur that endanger the health of the participant. In this case, the Ethics Committee of Hannover Medical School will be informed.

### Strategies to improve adherence to interventions {11c}

Prior to the commencement of the study, the entire research team underwent comprehensive training, which encompassed the principles of good clinical practice, the specifics of the study protocol, and the respective responsibilities of each team member.

A significant portion of the study is conducted online or via telemedicine, as patients with post-COVID-19 syndrome can exhibit considerable limitations in their resilience and mobility. As part of the study, only one on-site appointment is required. All other study assessments and treatments are completed online. This primarily includes the therapy appointments and the questionnaires used to assess the study outcomes. To facilitate patient convenience, the 50-min therapy sessions may be divided into two 25-min sessions. Patient reported outcome measures are also completed online, and respondents may interrupt and resume the questionnaires at their convenience. Additionally, the Physiotools app offers access to video demonstrations of therapeutic exercises from the field of exercise therapy, which can be viewed at any time.

### Relevant concomitant care permitted or prohibited during the trial {11d}

When a participant receives concomitant care that does not impair the ability to participate at the online-guided intervention, the study can be continued as planned. However, a simultaneous participation in a different trial focusing on the improvement of fatigue or quality of life is not possible. Additionally, participants are asked not to begin new treatments, unless they are urgently required for medical reasons. Changes in the therapy during the trial were documented.

### Provisions for post-trial care {30}

Post-trial care is not planned for this trial. If needed, patients will be referred to regular care that is available for post-COVID syndrome, i.e., physiotherapy, ergotherapy, or psychotherapy. The sponsor (Hannover Medical School) is providing an insurance, even without fault, to cover its liability as the requesting party in case of harm caused to the patient by participation in the study.

### Outcomes {12}

#### Primary outcome

This study examines the change in fatigue, as measured by the total score on the FAS [15], following a 3-month intervention period. The FAS is a 10-item assessment scale comprising 5 questions pertaining to physical fatigue and five questions (items 3, 6–9) pertaining to mental fatigue. Total scores range from 10 to 50. A total FAS score of less than 22 indicates the absence of fatigue, a score of 22 or above indicates the presence of fatigue, and a score of 35 or above indicates the presence of extreme fatigue.

#### Secondary outcomes

Health-related quality of life was assessed using the Short Form-36 Health Survey (SF-36) [16]. The 36 items comprising the SF-36 are designed to reflect eight domains of health, including physical functioning, physical role, pain, general health, vitality, social functioning, emotional role, and mental health. The range is 0–100, with higher scores indicating a superior quality of life. Furthermore, a physical and mental composite score can be calculated.Depression and anxiety, as measured by the Hospital Anxiety and Depression Scale (HADS-D) [17]: The HADS-D questionnaire comprises 14 items pertaining to the two subscales for anxiety and depression. Subscale scores range from 0 to 21, with higher scores indicating more severe anxiety or depression. Values can be interpreted as normal (0–7 points), mild (8–10 points), moderate (11–14 points), or severe (15–21 points).The degree of physical and psychological fatigue severity, as measured by the Chalder Fatigue Scale (CFS) [18]. The 11-part self-report instrument comprises a total scale and two subscales, namely physical and psychological fatigue. The maximum total score is 33, with higher scores indicating an increased level of fatigue. The maximum score for physical fatigue is 21, derived from seven items, while the maximum score for mental fatigue is 12, derived from four items. Furthermore, a binary code can be calculated for each of the 11 items (0 and 1 = 0; 2 and 3 = 1) in order to identify cases of severe fatigue. A total score of four or above is indicative of severe fatigue.Post-exertional malaise, as measured by the Post-Exertional Malaise Scale (PEM-Scale) [19]. The PEM-Scale employs five distinct 5-point Likert scales to quantify the frequency or severity of PEM symptoms and a 7-point Likert scale to assess the duration of PEM. This results in a maximum score of 46.Multidimensional fatigue, as measured by the Multidimensional Fatigue Inventory questionnaire (MFI-20) [20, 21]. The MFI-20 is a 20-item self-assessment instrument comprising five subscales: (1) general fatigue, (2) physical fatigue, (3) decreased activity, (4) decreased motivation, and (5) mental fatigue. Each subscale contains four items, with respondents indicating their level of agreement on a 5-point Likert scale (1 = strongly agree, 5 = strongly disagree). Higher scores indicate higher levels of fatigue.Disability, as measured by the Bell Disability Scale [22]. The Bell Disability Scale comprises 11 statements pertaining to the level of physical function. The scale is rated on a 10-point scale, with 0 indicating severe disability and 100 indicating full health.Work ability, as measured by the Work Ability Index (WAI) [23]. The WAI is a self-report questionnaire comprising seven items pertaining to work, work ability, and health. The total score, which ranges from 7 to 49, is interpreted as an indicator of work ability, with higher scores reflecting greater work ability.Illness perception, as measured by the Brief Illness Perception Questionnaire (IPQ) [24]. The IPQ is a tool designed to assess perceptions of cognitive and emotional illness. The abbreviated IPQ comprises 8 novel items and a portion of the causal scale that was previously employed in the IPQ-R. All items except the causal question are rated on a scale of 0 to 10. Five of the items assess cognitive representations of illness, namely consequences (item 1), time frame (item 2), personal control (item 3), treatment control (item 4), and identity (item 5). Two assess emotional representations: concern (item 6) and feelings (item 8). One item evaluates the comprehensibility of illness (item 7). An open-response item (item 9) requests patients to list the three most important causal factors for their illness.

### Participant timeline {13}

See Table 1.

**Table 1 Tab1:**
[figure not shown]
Schedule of enrollment, interventions, and trial assessments

### Sample size {14}

The sample size calculation is performed for the primary endpoint change from baseline to 3 months in the PCS fatigue symptoms estimated by the FAS. There is currently no published data available regarding the effect of a 3-month single psychotherapy or physical interventions compared to a combined approach on PCS fatigue-specific symptoms. Thus, the assumptions for the sample size calculation are based on preliminary data from a self-conducted pilot study (exercise therapy) and a trial by Kahlmann et al. (psychotherapy), in which a 3-month mindfulness-based, behavioral therapy in patients with chronic lung disease was investigated [8, 11]. A FAS change from baseline at 3 months of 2.0 (standard deviation (SD) = 5.0) for the physical therapy and 4.5 (SD = 5.8) for the psychotherapy, respectively, is assumed. Due to the fundamentally different therapy approaches, it is assumed that there will be more responders and less drop-outs in the combined therapy group compared to each monotherapeutic approach. Thus, a slightly additive effect of 7.0 with a SD of 5.0 is anticipated for the combination therapy. The sample size calculation is based on the comparison between the psychotherapy and the combined therapy approach since the difference of the FAS change for this comparison is assumed to be smaller than between the exercise and combination therapy. With a two-sided type-I-error of 5%, a power of 80%, a pooled SD of 5.0, and a difference of 2.5 in the FAS-change between psychotherapy and the combination therapy using a *t*-test for two independent samples, a sample size of *n* = 64 patients per group is required. With a Satterthwaite test assuming unequal variances (SD = 5.8 for the psychotherapy, SD = 5.0 for the combination therapy), a super additive effect of 7.2 would be necessary to achieve a power of 79.9% with the same sample size. Despite the co-primary group comparison approach, the power does not need to be increased to 90% because of the distinctly larger effect difference between the exercise therapy and the combination therapy (5.0). For a sample size of *n* = 64 patients per group, the power for this comparison of the single exercise therapy with the combination therapy would be > 99%.

To achieve a power of 80%, a total sample size of *n* = 195 patients (65 patients per group) is needed to demonstrate superiority of the combination therapy over monotherapeutic approaches. It is assumed that using an ANCOVA model adjusted for the stratification factors for the primary analysis will only increase the power compared to applying a *t*-test. All sample size calculations were performed using nQuery 9.2.1.0.

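### The 80% power uses a pooled SD of 5.0, but the plan's own SDs of 5.8 and 5.0 pool to 5.41, which gives about 74% at the planned difference

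*Protocol article*

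**What the plan says.** All the inputs are in the protocol article, Sample size {14}. For psychotherapy the assumed FAS change is "4.5 (SD = 5.8) for the psychotherapy, respectively, is assumed". For the combination, "a slightly additive effect of 7.0 with a SD of 5.0 is anticipated for the combination therapy". The planned difference is therefore 7.0 − 4.5 = 2.5.

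The calculation uses a two-sample t-test, two-sided 5% and 80% power, with "a pooled SD of 5.0, and a difference of 2.5 in the FAS-change between psychotherapy and the combination therapy", and concludes that "a sample size of *n* = 64 patients per group is required".

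The next sentence takes the two SDs as unequal (5.8 and 5.0) under a Satterthwaite test. It reports that a combined effect of 7.2 would then be needed for 79.9% power at the same sample size. It does not give the power at 7.0.

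The section's second paragraph returns to 80% power without qualification, for a total of 195 ("65 patients per group) is needed to demonstrate superiority of the combination therapy over monotherapeutic approaches". It adds that ANCOVA adjustment for the stratification factors can only raise the power relative to a t-test, but does not say by how much.

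**The concern.** A pooled SD lies between the SDs that go into it. It can equal 5.0 here only if both arms have an SD of 5.0, and the same paragraph puts psychotherapy at 5.8. The calculation therefore takes the more favourable of the two SDs and labels it pooled. The unequal-variance sentence shows that the difference was noticed, but it restores the power by enlarging the assumed effect and leaves the power at the planned effect unstated.

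This comparison matters most. Under Statistical methods {20a}, both co-primary comparisons must be significant for the trial to succeed. Exercise versus combination is planned on a difference of 5.0 with power above 99%, so psychotherapy versus combination in effect sets the power of the trial. If its power is overstated, a non-significant result will be read against a planning figure that the plan's own inputs do not support.

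**Working it through.** **Inputs** (all from Sample size {14}, except allocation, which is 1:1:1 in Trial design {8}): two-sided alpha 0.05; difference d = 2.5; SDs 5.8 (psychotherapy) and 5.0 (combination); n = 64 from the calculation and 65 planned per group.

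**Method.** Power comes from the non-central t distribution with non-centrality d / (SD × sqrt(2/n)) and 2n − 2 degrees of freedom. For the Satterthwaite test the non-centrality is d / sqrt(5.8²/n + 5.0²/n), with Satterthwaite degrees of freedom.

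**Step 1: reproduce the plan's figures.**
- d = 2.5, SD 5.0, n = 64: non-centrality 2.5 / (5.0 × sqrt(2/64)) = 2.83, power 80.1%. At n = 63 it is 79.5%, so 64 is confirmed.
- d = 7.2 − 4.5 = 2.7, SDs 5.8 and 5.0, n = 64, Satterthwaite: 79.9%, as stated.
- Exercise versus combination, d = 5.0, SD 5.0, n = 64: 99.99%, consistent with the stated figure of over 99%.

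Each figure follows from the inputs used for it, so the method matches the plan's. The question is only which SD was put in.

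**Step 2: pool the stated SDs.** With equal arms, sqrt((5.8² + 5.0²)/2) = sqrt((33.64 + 25.00)/2) = sqrt(29.32) = 5.41. Pooling all three arms, with 5.0 for exercise, gives sqrt((25 + 25 + 33.64)/3) = 5.28, which is still not 5.0.

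**Step 3: power at the planned difference of 2.5.**

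| SD used | n per group | Power |
|---|---|---|
| 5.0 (plan) | 64 | 80.1% |
| 5.41, t-test | 64 | 73.6% |
| 5.8 and 5.0, Satterthwaite | 64 | 73.6% |
| 5.41, t-test | 65 | 74.3% |
| 5.8 and 5.0, Satterthwaite | 65 | 74.3% |
| 5.28 (three arms pooled), t-test | 64 | 75.7% |

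The t-test and the Satterthwaite test agree, so the loss comes from the SDs and not from the choice of test. At 65 per group the type II error is 100 − 74.3 = 25.7%, against the intended 20%.

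**Step 4: size needed.** With d = 2.5 and these SDs, 80% power needs 75 per group, or 3 × 75 = 225 in total.

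**Step 5: both co-primary tests together.** Simulation of both tests under the stated means and SDs gave joint power of 73.7% at n = 64 and 74.2% at n = 65. The exercise comparison costs almost nothing.

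**Step 6: what ANCOVA would have to deliver.** To bring the residual SD from 5.41 back to 5.0, the covariates must remove 1 − 25/29.32 = 0.147 of the variance, a multiple correlation with FAS change of sqrt(0.147) = 0.38. The documents give no such correlation. Over an assumed range, power at n = 64 is:

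| Assumed multiple correlation | Power |
|---|---|
| 0 | 73.6% |
| 0.2 | 75.3% |
| 0.3 | 77.5% |
| 0.38 | 80.0% |
| 0.5 | 84.9% |

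**The case against.** Three points can be made for the plan.

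*The unequal-variance sentence already discloses the problem.* It uses exactly these SDs and says 7.2 would be necessary, so a careful reader can infer that 7.0 falls short. Solving for the required effect is also a recognised form of sensitivity check. This stands in part: 7.2 is in the text and correct. But the power at the planned 7.0 is never given, and the concluding statement of 80% does not carry the condition.

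*The primary analysis is not a t-test.* The ANCOVA in Statistical methods {20a} includes baseline FAS, which could recover the loss. If baseline and 3-month variances are equal (an assumption), the correlation of baseline with change has size sqrt((1 − r)/2), where r is the baseline-to-3-month correlation. It reaches 0.38 when r is about 0.71 or lower. At r = 0.5 it is 0.5 and power is about 85%; at r = 0.8 it is about 0.32 and power is about 78%. The planned analysis may therefore have more or less than 80% power. This stands as a limit on the finding: 74% is the power of the unadjusted test. It does not rescue the text, because the stated 80% is explicitly for a t-test, and the sample size section credits only the stratification factors without a figure.

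*The consequence is modest.* The estimand, model, type I error and success rule are untouched, the planning SDs are themselves uncertain, and a null result is better judged by its confidence interval. All true, but the finding does not dispute the SD assumptions. It says that the stated power does not follow from them.

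**Conclusion.** The concern holds. On the plan's own means and SDs, the limiting co-primary comparison has about 74% power with 65 per group (73.6% at 64), roughly 6 percentage points below the stated 80%. This rests on an unadjusted t or Welch test, complete data, equal arms and the stated planning values. The power of the planned ANCOVA cannot be derived from the document. It reaches 80% at 64 per group only if the covariates explain at least about 15% of the variance of FAS change.

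**What to change.** Revise Sample size {14} as follows:

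1. Stop describing 5.0 as the pooled SD. Either give the pooled value of 5.41 or say that 5.0 is an assumed common SD that is smaller than the psychotherapy assumption.
2. State that for combination versus psychotherapy, at the planned 7.0 with SDs 5.8 and 5.0 and 65 per group, the power of a t or Welch test is about 74%.
3. Keep 7.2 as the combined effect needed for about 80%, and attach that condition wherever 80% is claimed for 195 patients.
4. If the ANCOVA is relied on to restore power, state the assumed correlation of baseline FAS with FAS change, its source, and the resulting power.

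This is a change of wording only. The sample size, conduct and analysis can stay as they are. The cost is a less favourable stated power, and the results report should cite the same corrected figure.
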